### Study participants

Phase 1 workshop participants will be purposively selected hospital clinicians (doctors, pharmacists and nurses), primary care clinicians (GPs, community and credentialed pharmacists), and healthcare consumers, all having discharge medicine handover experience as either a clinician or end-user. Participants will be selected to ensure maximum variation (age, professional experience, role, gender). Allocation of participants to each group will be done in advance to avoid power imbalances [47].

Phase 2 will involve purposively selected hospital and primary care clinicians, managers and department heads, and software vendors to develop the intervention and handover guidelines/material for hospital and primary care clinicians. The digital solution will be pilot tested on selected general practices, community pharmacies, and a participating hospital.

The Australian Institute of Health and Welfare census data will be used to obtain population data for the areas serviced by the various hospitals to determine the number of suburbs for each hospital service area. Phase 3 will identify community pharmacy clusters whose population catchments, based on the suburb postcodes, capture community dwelling patients with high rates of 30-day readmission to hospital. Pharmacies and GP practices within those clusters will be invited into the study. Only pharmacies who consent to being involved will be recruited into the study. Once all pharmacies have consented, each pharmacy hub will be randomised to a different step in the stepped wedge design which will determine how long each hub will be in the control and intervention phase. The pharmacist navigator at each hospital will triage patients at risk of hospital readmission due to potential MRH by means of a risk stratification processes, use of local electronic medication record dashboards, and liaison with inpatient unit/ward pharmacists, nurse navigators, and other hospital clinicians.

Patients at risk of hospital readmission (according to the study developed risk stratification process) will be approached to be recruited to the study through the pharmacist navigator at each participating hospital.

Inclusion criteria:Ability to understand and the willingness to sign a written informed consent documentAge ≥ 18 years

Exclusion criteria:Receiving chemotherapyDischarging to an aged care facilityReceiving palliative care

The pharmacist navigator will use the risk stratification information to facilitate a structured handover of medicine information to patients’ community pharmacies, GPs, and credentialed pharmacists to trigger appropriate MMR services (Figs. 4 and 5).

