**Methods:**

A three-phased, multi-method study design is planned to trial a multifaceted intervention to reduce 30-day hospital readmissions. Phase 1 is the co-design of the intervention with stakeholders and end-users; phase 2 is the development of the intervention; phase 3 is a stepped wedge cluster randomised controlled trial with 20 clusters (community pharmacies). Expected intervention components will be a hospital pharmacist navigator, primary care medication management review services, and a digital solution for information sharing. Phase 3 will recruit 10 patients per pharmacy cluster/month to achieve a sample size of 2200 patients powered to detect a 5% absolute reduction in unplanned readmissions from 10% in the control group to 5% in the intervention at 30 days. The randomisation and intervention will occur at the level of the patient’s nominated community pharmacy. Primary analysis will be a comparison of 30-day medication-related hospital readmissions between intervention and control clusters using a mixed effects Poisson regression model with a random effect for cluster (pharmacy) and a fixed effect for each step to account for secular trends.

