**Fig. 1 Fig1:**
[figure not shown]
Multifaceted intervention

A hospital *pharmacist navigator* will facilitate a medicine handover at each of the participating hospitals. Navigators will work with the patient to connect with their nominated community pharmacy and GP. Using established medication management review *(MMR) services*, the patient’s medicines will be reconciled at the primary care level in the community pharmacy or in the patient’s home and follow-up actions communicated to the GP (Fig. 2). An innovative *digital solution* (Fig. 3) will link hospitals, community pharmacists, GPs, and patients together and, through asynchronous communication, provide all parties with information on all actions being performed throughout the transition of care.

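### The navigator who facilitates the intervention handover also triages and recruits patients after pharmacies are randomised, so the patient mix could differ by phase

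*Protocol article*

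**What the plan says.** Everything here is in the Protocol article.

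- **Unit.** Abstract, Methods: "The randomisation and intervention will occur at the level of the patient’s nominated community pharmacy".
- **Order of events.** Study participants: "Once all pharmacies have consented, each pharmacy hub will be randomised to a different step in the stepped wedge design". Patients are then enrolled individually, with written consent, at a target of 10 per cluster per month (Phase 3 sample size).
- **Selection.** Study participants: "The pharmacist navigator at each hospital will triage patients at risk of hospital readmission due to potential MRH". The means are a risk stratification process, electronic dashboards and "liaison with inpatient unit/ward pharmacists, nurse navigators, and other hospital clinicians".
- **Recruitment.** Same section: at-risk patients "will be approached to be recruited to the study through the pharmacist navigator at each participating hospital".
- **Delivery.** Multifaceted intervention text under Phase 3: "A hospital *pharmacist navigator* will facilitate a medicine handover at each of the participating hospitals", and "Navigators will work with the patient to connect with their nominated community pharmacy and GP". The abstract lists the navigator among the expected intervention components.
- **Blinding.** The only blinding stated is that of the panel that classifies readmissions (Primary outcome).
- **Model.** Data analysis names random effects for pharmacy and hospital and a fixed effect for step. It names no patient-level risk covariate.

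**The concern.** Randomising pharmacies balances pharmacies. It balances patients only if those who enter, and the pharmacy that sets their phase, do not depend on whether that pharmacy has crossed over. Here one role chooses whom to approach, is the route into the trial and facilitates the new service, all after allocation. If patients recruited in intervention months have a different baseline risk from those recruited in control months, the primary comparison mixes that difference with the treatment effect. A difference that starts at crossover within each pharmacy looks exactly like the intervention, and once enrolment is over it cannot be undone, only partly adjusted for.

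**Working it through.** **1. The plan's own figure.** 20 clusters × 10 patients per month × (12 − 1) months = 2200, as stated. The total is consistent. It relies on a monthly target per pharmacy, so the patient's pharmacy has to be known around enrolment.

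**2. Does the navigator know the phase?** This is not stated. The navigator facilitates the structured handover, and handover is part of what separates the phases. Someone doing that work has to know for which pharmacies it is due. I treat this as a strong inference.

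**3. What each stated safeguard covers.**

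| Safeguard | Protects | Leaves open |
|---|---|---|
| Risk stratification process | Narrows who is eligible | Ward liaison, the decision to approach, consent |
| Blinded panel | Classification of readmissions | Who is enrolled |
| Analysis by randomised crossover time | Cluster allocation | Which patients enrol, which pharmacy they nominate |
| Step, pharmacy and hospital effects | Secular trend, stable differences between pharmacies and hospitals | A shift that coincides with crossover within a pharmacy |

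**4. Why the model cannot separate the two.** Write log risk = pharmacy effect + step effect + θ·X, with X = 1 after crossover. If recruits after crossover have baseline risk multiplied by c, then log c attaches to X as well, and the model estimates exp(θ) = c × true RR. The step effect cannot absorb c, because in any one step some pharmacies have crossed over and others have not. The pharmacy effect cannot, because c changes within the pharmacy.

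**5. Size, as an illustration.** From the protocol article: 10% control risk and 5% intervention risk (Phase 3 sample size). Assumed, with no source in the article: half the eligible patients at 15% risk and half at 5%, so the mean is 0.5 × 15% + 0.5 × 5% = 10%. The true effect is set to zero.

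| High-risk share after crossover | Risk | Spurious RR |
|---|---|---|
| 45% | 0.45 × 15% + 0.55 × 5% = 9.5% | 0.95 |
| 40% | 0.40 × 15% + 0.60 × 5% = 9.0% | 0.90 |
| 60% | 0.60 × 15% + 0.40 × 5% = 11.0% | 1.10 |

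The 40% row is one of the five percentage points that the trial is designed to detect. With a true RR of 0.50, the estimate would be 0.90 × 0.50 = 0.45 in the 40% row and 1.10 × 0.50 = 0.55 in the 60% row.

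**6. Effect on the test.** Assume the stated ICC of 0.15, 8 evaluable patients per cluster-month (10 less 20%), four sequences (Fig. 1 is not shown) and a pharmacy effect that is constant over time. The standard error of the risk difference is then about 0.0259. For a spurious difference of 0.01, 0.01/0.0259 = 0.386, and the chance of a significant result is Φ(0.386 − 1.960) + Φ(−0.386 − 1.960) = 0.058 + 0.009 = 6.7% instead of 5%. Five or ten sequences give the same figure to within rounding. A shift of this size therefore distorts the estimate more than it inflates the false-positive rate.

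**7. What adjustment can do.** In step 5 the risk within each stratum is unchanged, so the RR is 15%/15% = 1 and 5%/5% = 1. A model that includes the stratum recovers the truth. It cannot do so for features that the score does not measure, such as engagement.

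**The case against.** The strongest reply is that this is a condensed article about an intervention still being co-designed. Order of approach, score cut-offs and screening logs commonly sit in the full protocol, and the flow and enrolment figures are not shown. Approach is tied to a study-developed risk stratification process, with no different rule given for the two phases. The patient nominates the pharmacy. Imputation of patient characteristics is planned, which suggests that covariates will be used. Much of this stands: the absence of a numeric cut-off or a log from the article is not itself an error. What remains is the assignment of roles, which the article does state. Triage, recruitment and handover are given to one role after allocation, and no analysis plan can change who was enrolled. Planning to impute characteristics is also not the same as naming a risk covariate in the primary model.

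Some stronger readings are tempting but unsupported:

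- **That the navigator takes consent, records the pharmacy or steers the nomination.** The text says only that patients are approached through the navigator, who works with them to connect with their pharmacy.
- **That the bias favours the intervention.** A navigator with a service to offer might favour the highest-risk patients, which pushes the estimate the other way (the 60% row above).
- **That such bias could reproduce the benefit reported in the literature.** The Background's RR of 0.81 is for all-cause readmission, while this trial's outcome is medication-related, so it is no yardstick here.

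**Conclusion.** The point holds as a risk to the primary comparison that arises from the roles as written. It is not a demonstrated bias. It rests on two stated facts (allocation precedes enrolment; one role triages, is the route to recruitment and facilitates handover) and one inference (that role knows which pharmacies have crossed over). None of the safeguards in the article covers it fully, although the risk stratification process reduces it. Size and direction are unknown. The RR of 0.90 depends entirely on assumed strata and an assumed ten-point fall in the high-risk share, and shows only that a modest shift in mix is visible against a five-point target. The matter deserves correction because it is cheap to address before enrolment and can be only partly repaired afterwards.

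**What to change.** In Study participants, state that:

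1. the same risk stratification cut-off applies in control and intervention phases;
2. eligible patients are approached consecutively in dashboard order until that cluster's monthly target is reached;
3. the patient's nominated pharmacy is recorded before its phase is looked up or the service is described, and the patient is analysed under that pharmacy without later change;
4. screened, eligible, approached and consented counts, with risk scores, are logged by cluster-month and reported by phase.

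In Data analysis, adjust the primary model for the baseline risk stratification score as logged at screening.

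Cost: wording, a screening log on the dashboards already in use, and one covariate; no extra staff. Navigators lose some discretion over whom to approach. The unit remains the nominated pharmacy. These steps do not make the recruiter unaware of phase, so consent may still differ between phases. The protocol should acknowledge that residual bias, and the log will let readers judge it.

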**Fig. 4 Fig4:**
[figure not shown]
Intervention flow diagram

**Fig. 5 Fig5:**
[figure not shown]
Trial SPIRIT [37] figure

There is no anticipated harm and compensation for trial participation.

### Study outcomes

#### Primary outcome

The primary outcome for the study is a comparison between intervention and control patients of (mean and median) unplanned hospital readmissions at 30-days post-discharge due to medicine-related harm as defined and ascertained below.

Hospital readmission events will be collected from the electronic medical record systems of the seven trial hospitals. The indexed admission will be any inpatient admission via any pathway (e.g. emergency department, elective surgery, outpatients) with an unscheduled representation to the emergency department within 30 days of discharge from the indexed admission. A panel consisting of four senior clinicians (emergency physician, geriatrician, specialist in general medicine, pharmacist) will consider each readmission event to determine if it is possibly medication related and assess its causality, severity, and preventability as MRH [48–50]. The panel will be blinded as to whether the readmission event came from an intervention or control cluster. Each event will be recorded by considering:What was the medicine?What was the event?Has the participant experienced MRH (doubtful, possible, probable or definite) [49]?

MRH will be defined as harm from non-adherence to a prescribed medicine, unintentional medicine error, or adverse medicine reaction [5, 51] within 30 days post-discharge from hospital. It will exclude intentional overdose or misuse but will include unintentional overdoses or misuse. Where the patient is considered to have experienced MRH (definite, probably and possible), the panel will further consider:Was the MRH preventable (definite preventable, possibly preventable, not preventable or unable to evaluate) [48, 49]?What was the severity (fatal, life-threatening, serious or significant) [50, 52]?What was the main cause (adverse drug reaction, unintentional error, non-adherence) [52]?

#### Secondary outcomes

Comparison between intervention and control patients (mean and median) of the proportion of patients with documented medicine handover in hospital electronic medical records when patients are discharged from hospital to primary care; data 3 months post completion of intervention of patients with a documented pharmacist and/or GP follow-up appointment organised prior to discharge from hospital through hospital medical records and follow-upComparison between intervention and control patients (mean and median) of completed post-discharge MMR services and medicine reconciliation by community and credentialed pharmacists; data 3 months post completion of intervention through self-reported survey of primary care pharmacistsMode of medicine information communication (i.e. phone, fax, email, etc.) between primary care clinicians; data 3 months post completion of intervention through GP practice and pharmacy notes and survey of primary care pharmacistsUse of digital solution for medicine handover communication from hospital to primary care clinicians and between primary care clinicians; data 3 months post completion of intervention through digital data recordsPatients’ self-reported understanding of their medicines, how to take them and quality of life; telephone survey within 30 days post-discharge of patients (control and intervention groups; mean and median) incorporating EQ-5D-5L [53] questions, hospital service utilisation since discharge, self-reported understanding of medicines, and feedback on the multifaceted interventionHealthcare usage economic analysis through a stepped cost-effectiveness/cost-utility analysis that will evaluate the implementation of the navigator, the MMR, and the digital medicine handover solution as a single package of care. The costs of the package of care will include the salary costs of the navigator and of the pharmacist conducting MMR services, costed using standard pay scales and including on-costs. The cost of the digital medicine handover solution will be considered in terms of the cost of rolling it out more broadly (i.e. development costs will be noted but not included in the economic evaluation itself). The cost of readmissions in both arms will be included, potentially offsetting some of the package cost with data from the participating hospitals and/or diagnosis-related group information. As 30-day readmissions are the primary focus of the clinical evaluation, we will explore the sensitivity of assuming an ongoing difference in readmission risk in a scenario analysis. We will also include the cost of other healthcare services, such as medicine use, and outpatient visits (both to the hospital and primary care) costed using standard Pharmaceutical Benefits Scheme/Medicare Benefits Scheme/hospital rates. Finally, we will include costs to patients and carers of receiving care, with a tailored questionnaire designed to capture costs associated with travel, parking, and employment losses. This can be used to estimate a societal economic evaluation

Regarding outcomes, we will first present cost per readmission avoided, reflecting our proposed primary outcome. We will then generate a cost-utility analysis through combination of the cost data described above with information around mortality and quality of life (captured using the EQ-5D-5L [53]) to generate a cost per quality-adjusted life year (QALY) of the package relative to usual care. Standard univariate and probabilistic sensitivity analysis will be conducted to identify key drivers of the results of the economic evaluation, and to suggest factors to which the result is most sensitive and hence appropriate for future research.7.Acceptability and fidelity of the multifaceted intervention [54] gathered through semi-structured interviews with participating clinicians up to three months post completion of intervention. We will incorporate a thorough process evaluation to assess how the intervention was delivered to provide policymakers and practitioners with vital information about how the intervention could be replicated. A process evaluation also provides generalisable knowledge on how to implement complex interventions [54]. An acceptability framework survey will be used to obtain feedback from clinicians on the intervention [55, 56]. We will also purposively select clinicians for semi-structured interviews for qualitative feedback, with participants selected to achieve maximum variation (profession, role, gender, hospital or clinic). Issues explored through the survey and interviews will include:◦ Overall acceptability for clinicians◦ Burden (i.e. reasons given for discontinuation and/or dropout)◦ Ethical consequences (i.e. associated side effects with intervention)◦ Experience (i.e. user experience, user perceptions, satisfaction)◦ Affective attitude (i.e. attitude towards intervention, attitude measures)◦ Opportunity costs (i.e. influence on adherence, and participation)◦ Intention (i.e. willingness to participate in the intervention)◦ Perceived behavioural control (i.e. the extent to which the individual believes they have autonomy/control over the situation wherein the intervention takes place)◦ Perceived treatment control (i.e. the extent to which the individual believes the treatment will be effective in curing the illness/helping the patient)

### Data analysis

Phase 1 and 2 qualitative data will be thematically analysed [57, 58]. Audio recordings will be professionally transcribed verbatim by an independent party and the transcripts quality screened and cross-referenced. The NVivo© software (QSR International Pty Ltd, Chadstone, Australia) will be used for coding by two coders. Where there are differing interpretations, the differences will be discussed between the members of the research team until consensus is reached. Data will be thematically analysed to identify underlying themes.

All phase 3 participants (excluding those recruited in the lead-in phase) will be included in the analysis. Each cluster will be classified as being in the intervention or the control phase based on their pre-specified randomised crossover time, regardless of whether crossover is achieved at that time. In the primary analysis, overall differences in readmissions will be modelled using a mixed effects Poisson regression model with a random effect for cluster (pharmacy) and a fixed effect for each step to account for any secular trend. Secular trends may include seasonal variation in readmissions or changes in practice (outside of the project’s control). We also intend to allow for both levels of clustering at the analysis stage, i.e. we will allow for both clustering by hospital and clustering by pharmacy (the unit of randomisation). This will be achieved by including both a random effect for community pharmacy hub and a random effect for hospital. Robust standard errors will be used to allow for the misspecification of the error structure when using the Poisson model to model binary events. We will report treatment effects both on the relative and absolute scale. We will also report estimates of intra cluster correlations. Secondary analysis will be conducted using similar techniques. The primary and secondary outcomes will be considered significant at the 5% level, and 95% confidence intervals will be reported. Missing outcome data is likely to be minimal for this study as it is routinely collected through hospital records. If the level of missing patient characteristic data is above 5%, we will use multiple imputation methods which allow for clustering and time effects. We will not conduct an interim analysis.

Development of phase 3 patient telephone surveys, clinician interview guides, and project data collection forms at hospital and community pharmacy levels will be guided by the Consolidated Framework for Implementation Research [59, 60]. The framework will be used to guide data collection, coding, analysis, and reporting of findings to obtain insights into the fidelity of implementation of each component of the intervention, including interprofessional communication and patient and health professional satisfaction with service(s) provided. The COREQ checklist and qualitative research criteria will be used in the development, analysis, and reporting of the phase 1 qualitative workshop data and phase 3 interviews with clinicians and patients [61, 62].

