#### Phase 3: Stepped wedge cluster randomised controlled trial (SW-CRT) of newly designed intervention over 12-month period

We will perform a 12-month SW-RCT [44], comparing the intervention with standard care. Twenty clusters of community pharmacies will be pragmatically allocated to receive the intervention. Data will be collected from all clusters over the study period. Each cluster will provide before and after intervention data. This study design is represented in Fig. 1. The anticipated date of first enrolment is 1 October 2025, and last day for recruitment is 30 September 2026.

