### Phase 3 sample size

The phase 3 sample size was calculated for the primary outcome, taking into account the intracluster correlation coefficient (ICC), the expected baseline number of readmissions, effect of the intervention, and the desired power of the study (power = 80%, *α* = 0.05) [44, 45]. Patterns of ICCs were drawn from other sources [27, 46] to assume an ICC of 0.15. Based on previous studies [27, 28], it is estimated there will be a reduction in unplanned readmissions from 10% in the control group to 5% in the intervention at 30 days. With an expected 20% drop out rate and aiming for 90% power, we aim to recruit 10 patients per pharmacy cluster per month which will provide a total sample size of 2200 (excluding the cluster lead-in period).

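### The claim that missing outcome data will be minimal holds only for record-based outcomes, and the stated imputation rule does not reach the patient survey outcomes

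*Protocol article*

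**What the plan says.** All references are to the protocol article.

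- **Data analysis, extent of missing outcomes:** "Missing outcome data is likely to be minimal for this study as it is routinely collected through hospital records". The sentence speaks of the study as a whole and comes directly after one on the significance level for primary and secondary outcomes.
- **Data analysis, imputation:** "If the level of missing patient characteristic data is above 5%, we will use multiple imputation methods which allow for clustering and time effects". No rule for missing outcomes is given. The section also says that all phase 3 participants outside the lead-in will be analysed and that secondary analyses will use similar techniques.
- **Primary outcome:** readmission events are taken from the electronic records of the seven trial hospitals.
- **Secondary outcomes:** quality of life and understanding of medicines come from a "telephone survey within 30 days post-discharge of patients (control and intervention groups; mean and median"), which includes the EQ-5D-5L and asks about hospital use since discharge. Completion of medication management reviews comes from a survey of primary care pharmacists. The EQ-5D-5L is later combined with costs and mortality to give a cost per QALY.
- **Phase 3 sample size:** "With an expected 20% drop out rate and aiming for 90% power". The text does not say what the patients drop out of.

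**The concern.** The expectation of near-complete outcome data rests on one reason: the data come from hospital records. Several secondary outcomes do not come from there. The patient-reported ones exist only if the patient answers a telephone survey after discharge, and completion of reviews is known only if the pharmacist reports it. For these outcomes the premise is wrong, and the missing-data rule built on it covers patient characteristics alone.

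The comparison at stake is quality of life, and through it the cost per QALY. Patients are selected for their risk of readmission, and the survey falls in the same 30 days in which readmission is counted. If readmitted patients answer less often, an analysis of responders removes proportionally more poor outcomes from the condition with more readmissions. On the plan's own expectation that is the control condition.

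**Working it through.** **1. Reason against source.**

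| Outcome | Source in the article | Does the hospital-records reason apply? |
|---|---|---|
| 30-day readmission | Hospital electronic records | Yes |
| EQ-5D-5L, understanding of medicines, self-reported hospital use | Patient telephone survey | No |
| Completed medication management reviews | Survey of primary care pharmacists | No |

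The imputation trigger (more than 5% missing) applies to patient characteristics, so it reaches neither row marked No.

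**2. The plan's own figures.** 20 clusters × 10 patients per month × (12 − 1 lead-in) months = 2200, which reproduces the stated total. After 20% drop-out, 2200 × 0.80 = 1760 remain and 440 are lost. The section says the sample size was calculated for the primary outcome, so there are two readings:

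- If the 20% refers to the record-based primary outcome, it conflicts with an expectation of minimal missing data.
- If it refers to the survey (an assumption), 440 of 2200 is 20%, four times the 5% at which the plan would impute characteristics.

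**3. Illustration of bias.** From the plan: readmission p = 10% in control and 5% in intervention. Assumed, because the article gives no values: utility 0.50 if readmitted and 0.75 if not; 85% response in patients not readmitted; response r in readmitted patients, the same in both conditions.

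True readmission-driven difference = (0.75 − 0.50) × (0.10 − 0.05) = 0.0125.

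Share of readmitted patients among responders: f(p) = p·r / [p·r + (1 − p)·0.85]. Responder-only difference = 0.25 × [f(0.10) − f(0.05)].

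| r | f(0.10) | f(0.05) | Difference | Too small by |
|---|---|---|---|---|
| 0.85 | 0.1000 | 0.0500 | 0.0125 | 0% |
| 0.70 | 0.070/0.835 = 0.0838 | 0.035/0.8425 = 0.0415 | 0.0106 | 15% |
| 0.50 | 0.050/0.815 = 0.0613 | 0.025/0.8325 = 0.0300 | 0.0078 | 37% |
| 0.40 | 0.040/0.805 = 0.0497 | 0.020/0.8275 = 0.0242 | 0.0064 | 49% |

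**4. Cross-check with another loss pattern.** Fix overall survey loss at 20% in each condition and let a share L of readmitted patients be lost. Then f(p) = p·(1 − L)/0.80, and the fraction of the difference retained is (1 − L)/0.80. This gives 100% at L = 20%, 75% at L = 40%, 50% at L = 60% and 0% at L = 100%. The proportion retained does not depend on the assumed utilities.

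**5. Absolute size.** At r = 0.50 the shortfall is 0.0125 − 0.0078 = 0.0047 in utility. Held for 30 days, that is 0.0047 × 30/365 ≈ 0.0004 QALY per patient.

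**The case against.** The strongest reply is that the sentence was meant for record-based outcomes, as its own reason suggests, and that handling of missing survey data is normally left to the statistical or health-economic analysis plan. Part of this stands: an unseen plan may contain a rule, and the absence of detail would not be a finding. But the article does more than stay silent. It states a premise for the whole study that fails for named outcomes, and it sets an imputation rule that leaves those outcomes out.

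Four stronger readings are tempting and are not supported:

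- **That the survey will lose the readmitted patients.** The article gives no response rate and no reasons for loss. The survey asks about hospital use since discharge, so readmitted patients are meant to be included.
- **That the plan expects 20% survey loss.** The figure belongs to the sample size for the primary outcome and is not tied to the survey.
- **That deaths fall out of the QALY analysis.** The Secondary outcomes section brings mortality in alongside quality of life. What remains is only that the handling of deaths should be explicit.
- **That the bias has a known size.** The percentages rest on assumed response rates, and the absolute shortfall is small. If non-response is unrelated to readmission, this bias is zero.

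**Conclusion.** The point holds for secondary and economic outcomes. The expectation of minimal missing data is justified by its stated reason only for outcomes taken from hospital records, and the plan as written leaves patient survey outcomes to an analysis of responders. The sentence also sits badly beside the 20% drop-out, whichever way that figure is read.

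Whether bias follows depends on whether non-response is related to readmission, which is plausible but undocumented. If it is, and if readmitted patients have lower utility and the intervention reduces readmission, the readmission-driven part of the quality-of-life difference shrinks towards zero: by 15% to 49% over 70% to 40% response among readmitted patients under the assumptions above, and by nothing at equal response. In that setting the bias hides benefit and does not create it. The primary outcome is not affected by survey non-response. The correction should be made, but it does not threaten the trial's main conclusion.

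**What to change.** 1. Limit the statement on minimal missing data to outcomes taken from hospital records.
2. Reconcile it with the 20% in Phase 3 sample size: say what patients drop out of, and that loss to the telephone survey does not remove a patient from the record-based primary outcome.
3. Extend the multiple imputation already planned, allowing for clustering and time, to the patient survey outcomes. Use 30-day readmission status from the records, phase, step and pharmacy as predictors, and add other variables only where they are actually recorded. Readmission status is available for survey non-responders. In the illustration, where response depends on readmission alone, conditioning on it removes the bias.
4. Add a sensitivity analysis for loss related to readmission or death, and state how deaths enter the quality-of-life comparison.

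The cost is a change of wording and modest extra analysis work. No extra patient contact is needed, and the change can be made before the first enrolment, planned for 1 October 2025.
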